#### **Primary Endpoint Analysis**

- Incidence of thromboembolic events will be compared between ICE and TEE groups.
- Analysis will use logistic regression to estimate the risk difference and 95% confidence interval.
- Non-inferiority is demonstrated if the upper bound of the 95% CI for the risk difference is below the predefined margin of 0.8%.
- The primary endpoint was evaluated using risk difference (RD) with Farrington – Manning 95% CI, and noninferiority was concluded if the upper CI limit was below the prespecified margin.

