#### 3.2 Sample size justification

The sample size calculation is based on the hypothesis and study design. For this non-

inferiority trial, the following parameters were used:

Type I error ( $\alpha$ ) = 0.025, corresponding to a Z-value ( $Z_{\alpha}$ ) of 1.96

Type II error ( $\beta$ ) = 0.2, corresponding to a Z-value ( $Z_{\beta}$ ) of 0.84

Expected event rate in the ICE group ( $p_1$ ) = 0.6%

Expected event rate in the TEE group ( $p_2$ ) = 0.5%

Non-inferiority margin ( $\Delta$ ) = 0.8%

These values were plugged into the sample size calculation formula for non-inferiority studies:

$$n = (Z_{\alpha} + Z_{\beta})^2 \cdot (p_1(1 - p_1) + p_2(1 - p_2)) / (p_1 - p_2 - \Delta)^2$$

$$n = (1.96 + 0.84)^2 \cdot (0.006(1 - 0.006) + 0.005(1 - 0.005)) / (0.006 - 0.005 - 0.008)^2$$

$$n = 7.84 \cdot (0.006 \cdot 0.994 + 0.005 \cdot 0.995) / (-0.007)^2$$

$$n = 7.84 \cdot 0.010939 / 0.000049$$

$$n = 1750.45$$

Based on this calculation, a sample size of approximately 1750 patients is required to achieve 80% power at a 5% significance level, assuming a non-inferiority margin of 0.8%. The actual recruited sample size of 1810 patients is slightly higher than the calculated sample size, indicating that the study's statistical power might be slightly higher than the anticipated 80%.

If the expected dropout rate is 2%, the sample size should be adjusted accordingly. The adjusted sample size can be calculated using the following formula: Adjusted sample size = Original sample size / (1 - Dropout rate)

In this case, the original sample size is 1750 patients (875 in each group). Applying the dropout rate adjustment: Adjusted sample size =  $1750 / (1 - 0.02) = 1750 / 0.98 = 1786$  (rounded up).

Therefore, to maintain the desired statistical power and significance level while accounting for the expected 2% dropout rate, a total of 1786 patients (approximately 893 in each group) should be recruited.

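### The primary analysis is specified twice, as a logistic-regression risk difference and as a Farrington-Manning interval, and with about 10 events expected the two can give opposite non-inferiority conclusions

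*Protocol*

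**What the plan says.** Three statements under Primary Endpoint Analysis in Section 5.4 (Statistical Methods) bear on this point.

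- Method, first statement: "Analysis will use logistic regression to estimate the risk difference and 95% confidence interval". No covariates are given, nor any conversion from the odds scale.
- Decision rule: "Non-inferiority is demonstrated if the upper bound of the 95% CI for the risk difference is below the predefined margin of 0.8" (per cent).
- Method, second statement: "The primary endpoint was evaluated using risk difference (RD) with Farrington – Manning 95% CI", again with non-inferiority read from the upper limit against the margin.

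The logistic bullet is in the future tense and the Farrington-Manning bullet in the past, but the text does not say that one replaces the other. The paragraph on subgroup and sensitivity analyses lists only the exclusion of equivocal imaging and procedural adherence, so it does not rank the two methods. The headings of Section 8, which lists the modifications, include none for the primary analysis.

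**The concern.** One endpoint and one decision rule have two methods and therefore two possible upper limits.

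The first method is also incompletely specified. Logistic regression yields a log odds ratio. A risk difference needs a further step, such as standardisation with a delta-method or bootstrap interval, and none is given. With treatment as the only term, the fitted risks are the observed proportions and the delta-method interval is the ordinary Wald interval. If an arm has no events, the logistic coefficient has no finite estimate.

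With so few events the choice of interval can decide the result. The trial is open-label, so the choice could be made once event counts are known. If the looser interval is used, the chance of wrongly declaring non-inferiority exceeds the 2.5% set in Section 3.2.

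**Working it through.** **Inputs.** Section 3.2: ICE rate 0.6%, TEE rate 0.5%, margin 0.8 percentage points, one-sided α 0.025 (z = 1.96), β 0.2. Sections 1.2 and 2.3: 1810 patients randomised 1:1, so 905 per arm. Expected events: 905 × 0.006 + 905 × 0.005 = 5.43 + 4.53 = 9.96.

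**The protocol's own figure.** 7.84 × (0.006 × 0.994 + 0.005 × 0.995) / 0.007² = 7.84 × 0.010939 / 0.000049 = 1750.24. The protocol prints 1750.45, which is immaterial. The variance in this formula is unpooled, that is, of Wald type.

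**The two upper limits.** Let d be the observed difference, ICE minus TEE.

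- Unadjusted logistic with delta method (Wald): d + 1.96 × √[p₁(1−p₁)/n + p₂(1−p₂)/n], with p₁ and p₂ the observed proportions.
- Farrington-Manning: the score statistic z = (d − 0.008)/SE₀, where SE₀ uses the maximum-likelihood proportions restricted to differ by 0.008. The upper limit is below 0.8% only if z < −1.96.

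**Worked case: 5 ICE and 4 TEE events, 905 per arm.**

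- p₁ = 0.005525, p₂ = 0.004420, d = 0.001105.
- Wald: SE = √[(0.005494 + 0.004400)/905] = 0.003307. Upper limit = 0.001105 + 1.96 × 0.003307 = 0.00759, or 0.759%. Non-inferior.
- Farrington-Manning: restricted proportions 0.010948 and 0.002948. SE₀ = √[(0.010828 + 0.002939)/905] = 0.003900. z = (0.001105 − 0.008)/0.003900 = −1.77, which does not reach −1.96. Inverting the score test gives an upper limit of 0.897%. Not shown.

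**Other splits at 905 per arm.**

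| ICE / TEE events | Wald upper limit | Farrington-Manning upper limit | Conclusions |
|---|---|---|---|
| 4 / 3 | 0.682% | 0.837% | opposite |
| 5 / 4 | 0.759% | 0.897% | opposite |
| 5 / 5 | 0.683% | 0.8001% | opposite, but borderline |
| 6 / 6 | 0.748% | 0.855% | opposite |
| 4 / 6 | 0.462% | 0.548% | both non-inferior |
| 6 / 4 | 0.904% | 1.049% | both not shown |

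**Exact operating characteristics.** These sum the two binomial distributions over event pairs at 905 per arm. The 0.2% TEE rate is an assumption made here for illustration; the protocol does not give it.

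| True ICE / TEE rate | Wald declares non-inferiority | Farrington-Manning declares non-inferiority |
|---|---|---|
| 0.6% / 0.5% (planned) | 53.5% | 39.2% |
| 1.3% / 0.5% (at the margin) | 3.4% | 1.9% |
| 1.0% / 0.2% (at the margin, assumed) | 4.5% | 1.7% |

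At the planned rates the rules disagree in 14.2% of trials. In every discordant pair the Wald rule passes and Farrington-Manning fails. Given exactly 10 events, they disagree in 23.7%.

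**No events in the TEE arm.** 0.995⁹⁰⁵ = 1.1% at the planned rate; 0.998⁹⁰⁵ = 16% at the assumed 0.2%.

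**The case against.** The strongest reply is that the protocol really names only one interval. On this reading the logistic bullet is loose wording that shares the estimand, margin and rule with the Farrington-Manning bullet, and a statistical analysis plan may settle the matter. It is true that only one bullet names an interval method. But the other says that logistic regression will supply the confidence interval, and a plan that chose either method would contradict a sentence of the protocol.

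Other points have substance:

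- The 5/5 split is too close to rely on. Farrington-Manning gives 0.8001% at 905/905 but 0.798% at 906/904, and simple randomisation need not produce equal arms. That cell contributes about 3.0 of the 14.2 points, so about 11 remain without it. The 4/3, 5/4 and 6/6 splits are clear.
- The logistic figures depend on an unadjusted model with a delta-method interval. Covariates or a bootstrap would change them, but would also add choices that the protocol does not make.
- The two rules agree in about 86% of trials at the planned rates, and Section 4.2 keeps the analysts blinded during the primary analysis. This limits an outcome-driven choice but does not exclude it.
- The zero-event problem is minor at the planned rate (about 1%), and the risk difference itself remains defined.

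**Conclusion.** The concern holds. The protocol gives two unranked methods for one confirmatory decision, and they reach opposite conclusions at event counts close to those it expects. At 905 per arm and the planned rates this affects 14.2% of trials, always in favour of declaring non-inferiority by the logistic/Wald route. That route has a one-sided error of 3.4% at the margin with TEE at 0.5%, while Farrington-Manning stays below 2.5% in both margin scenarios checked. The sizes rest on equal arms of 905, complete outcome data and an unadjusted logistic model with a delta-method interval. The contradiction itself rests on none of these. It should be corrected before the primary analysis, because the trial's conclusion can turn on it.

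**What to change.** Delete the logistic-regression bullet. State one primary analysis: the unadjusted risk difference, ICE minus TEE, with the two-sided 95% Farrington-Manning interval (restricted-likelihood score), and its upper limit compared with 0.8%. State also whether the reported limit comes from inverting the score test or from the restricted standard error at the margin. For 5/4 events these print 0.897% and 0.875%, but both turn on the same z at 0.8% and so give the same decision. If a regression model is still wanted, label it supportive and give it no part in the decision; a Firth-penalised odds ratio is one option that copes with an arm without events.

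The edit is a line or two of text. Its consequence is larger, because Section 3.2 sizes the trial with a Wald-type variance and the sample size must be rechecked for the interval chosen. At 905 per arm the chance of success at the planned rates is 39.2% with Farrington-Manning and 53.5% with Wald. Both fall well short of 80%, chiefly because the formula in Section 3.2 gives a number per group that the protocol uses as the total. That is a separate matter and needs its own correction.

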#### **Secondary Endpoint Analysis**

- 508 • Continuous variables (e.g., procedure time, pain scores): Presented as mean  $\pm$   
509 SD or median (IQR); Compared using t-test or Wilcoxon rank-sum test  
510 (based on normality).
- 511 • Categorical variables (e.g., thrombus detection, bleeding): Expressed as counts  
512 and percentages and compared using chi-square or Fisher's exact test.
- 513 • Binary secondary endpoints were reported as relative risk (RR) with 95% CIs;  
514 continuous endpoints were expressed as mean difference (MD) with 95% CIs.
- 515 •

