## 2.3 Trial Design

This study is a multicenter, prospective, randomized, open-label, parallel-group, non-inferiority trial. A total of 1810 patients undergoing AF ablation were randomized 1:1 to receive either ICE-guided or TEE-guided thrombus screening. Outcome assessors, including the Clinical Endpoint Committee (CEC), are blinded to group allocation.

[figure not shown]

Figure 1. Trial design

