### 3. Methods: Participants, Sample size justification , Interventions, and Endpoints

#### 3.1 Study Setting

This multicenter study was conducted at 10 tertiary medical institutions across China, including Shanghai Chest Hospital, Ren Ji Hospital, and eight additional high-volume centers specializing in AF ablation (see Appendix for full list of participating sites). All centers possess substantial expertise in AF ablation and intracardiac imaging, thereby ensuring strict adherence to the study protocol and high procedural quality.

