## Secondary Endpoints

The prespecified secondary endpoints include:

- The detection rate of thrombus.
- Death related to the radiofrequency ablation procedure.
- Major bleeding complications: pericardial effusions and cardiac tamponade.
- Minor bleeding complications: vascular complications such as pseudoaneurysms, arterio-venous fistulas, and hematomas.
- Procedural characteristics: total procedure time, fluoroscopy time, and radiofrequency delivery time.
- Pre-procedural psychological state: Assessed using the Hospital Anxiety and Depression Scale (HADS), 14a self-assessment questionnaire measuring anxiety and depression levels in patients receiving medical care. Higher scores indicate more severe symptoms.
- Procedural pain degree: Measured using the Numeric Rating Scale (NRS), where patients rate their pain on a scale from 0 (no pain) to 10 (worst possible pain).
- Hospitalization cost: Expenses incurred during a patient's hospital stay, including charges for medical services, procedures, medications, accommodations, and other related expenses.
- Preprocedural waiting time: The period of time a patient waits before undergoing ablation.

These well-defined endpoints will help the researchers assess the effectiveness, safety, and patient experience of using ICE compared to TEE in patients undergoing AF ablation.

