## 4. Methods: Assignment of Interventions

### 4.1 Allocation

This study employs a **simple computerized randomization** strategy with a 1:1 allocation ratio. Eligible participants are randomly assigned to undergo thrombus screening with either ICE (ICE group) or TEE (TEE group) before catheter ablation.

The randomization schedule is generated using validated, centralized computer software to ensure adequate allocation concealment. Allocation occurs **after patient enrollment and informed consent**, and prior to the start of imaging and ablation procedures.

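### Continuous secondary endpoints: the p-value may come from a rank test while the interval is always for a mean difference, so the two can disagree

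*Protocol*

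**What the plan says.** Under Secondary Endpoint Analysis in section 5.4 (Statistical Methods), the protocol has continuous variables "Compared using t-test or Wilcoxon rank-sum test", the choice being made "based on normality". It names no normality criterion and does not assign endpoints to tests. A later bullet in the same list states that "continuous endpoints were expressed as mean difference (MD) with 95% CIs". That effect measure applies whichever test is used, and no other estimate is named to go with Wilcoxon.

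Section 3.5 lists the endpoints concerned: "total procedure time, fluoroscopy time" and radiofrequency time, HADS score, 0-10 pain rating, hospitalization cost and preprocedural waiting time.

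Three design facts matter for the working. Section 2.3 states "A total of 1810 patients undergoing AF ablation were randomized 1:1". Section 4.1 specifies "simple computerized randomization", with no stratification by centre stated. Section 3.1 says the study was "conducted at 10 tertiary medical institutions across China". Neither of the two named tests carries a centre term.

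**The concern.** A t-test and a mean difference belong together: the test rejects exactly when the matching interval excludes zero. A Wilcoxon test and a mean difference do not. The rank test asks whether a value in one arm tends to exceed a value in the other; the interval asks whether the means differ. For skewed outcomes these can have different answers.

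The protocol fixes both the switch and the effect measure, so an analysis plan that follows it inherits the mismatch. A reader could meet a significant p-value beside an interval that includes zero, or the reverse, with nothing to say which governs. Because the choice depends on the observed data without a stated criterion, it also leaves the analyst discretion after the data are in.

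**Working it through.** The protocol gives no SD, power or variance component for these endpoints, so there is no figure of its own to reproduce. The check has three steps.

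**Step 1: do the two quantities test the same thing?** They do if the arms are identically distributed or differ only by a shift. Otherwise they need not. Example with log-normal data, where mean = exp(μ + σ²/2) and median = exp(μ):

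- Arm A, μ = −0.18, σ = 0.6: mean = exp(−0.18 + 0.36/2) = 1; median = exp(−0.18) = 0.835.
- Arm B, μ = −0.125, σ = 0.5: mean = exp(−0.125 + 0.25/2) = 1; median = exp(−0.125) = 0.882.

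The true mean difference is zero, yet values in arm A tend to be lower. Different spreads are not far-fetched here: under section 3.4 the ICE arm uses a minimised-fluoroscopy strategy, while the TEE arm has fluoroscopy-guided transseptal puncture.

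**Step 2: how often would they disagree?** Simulation with 1810/2 = 905 per arm and 2000 runs per row. Assumption: a Shapiro-Wilk test at 5% in either arm triggers Wilcoxon; otherwise a Welch t-test is used. The effect rows use a shift of 2.8 × SD × √(2/905) = 0.132 SD, on the log scale for log-normal data. That is about 80% power on the log scale. The pain score is a normal variable (mean 3, SD 2) rounded and limited to 0-10. Disagreement means that the chosen p < 0.05 and the 95% CI for the mean difference excluding zero do not coincide.

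| Scenario | Wilcoxon rejects | Mean difference rejects | Disagree |
|---|---|---|---|
| Pain score, no effect | 5.4% | 5.0% | 1.4% |
| Log-SD 0.3, no effect | 5.1% | 5.3% | 2.9% |
| Log-SD 0.5, no effect | 5.3% | 5.7% | 4.4% |
| Log-SD 0.8, no effect | 6.5% | 5.2% | 5.9% |
| Log-SD 1.0, no effect | 5.5% | 5.3% | 6.8% |
| Pain score, effect | 77.4% | 78.8% | 4.8% |
| Log-SD 0.3, effect | 78.4% | 79.0% | 7.4% |
| Log-SD 0.5, effect | 76.8% | 73.3% | 11.6% |
| Log-SD 0.8, effect | 78.3% | 63.9% | 22.6% |
| Log-SD 1.0, effect | 78.5% | 56.4% | 29.4% |
| Equal means, unequal spread (step 1) | 53.5% | 4.8% | 52.5% |

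Normality was rejected in every run, so Wilcoxon was always the chosen test. Where the true mean difference is zero, the mean-based test rejects in 4.8% to 5.7% of runs. The Monte Carlo standard error at 5% is √(0.05 × 0.95/2000) = 0.5 points, so mean-based inference holds its level at this sample size even with marked skew.

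**Step 3: what would a centre term add?** Under individual randomisation, if a share ρ of the outcome variance lies between centres, adjustment multiplies the variance by about (1 − ρ), so the interval width is multiplied by √(1 − ρ). The last column is Φ(2.80/√(1 − ρ) − 1.96).

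| Assumed ρ | √(1 − ρ) | CI narrower by | 80% power becomes |
|---|---|---|---|
| 0.01 | 0.995 | 0.5% | 80.4% |
| 0.05 | 0.975 | 2.5% | 82.0% |
| 0.10 | 0.949 | 5.1% | 84.0% |
| 0.20 | 0.894 | 10.6% | 87.9% |
| 0.30 | 0.837 | 16.3% | 91.8% |

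A ten-centre simulation (500 runs) gave standard-error ratios of 0.98 at ρ = 0.05 and 0.86 at ρ = 0.20, broadly in line.

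**The case against.** **No formal normality test is named.** This is correct. The judgement could be graphical or set per endpoint in an analysis plan that is not shown, so the 100% rejection rate belongs to the assumed test and distributions. The mismatch remains for any endpoint that ends up with Wilcoxon, since the protocol attaches a mean difference to all of them.

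**The disagreement rates are constructed.** This is also fair. Without an effect they are small. The high values need strong skew together with a moderate effect, or unequal spread. They show what can happen, not what will.

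**Other coherent pairings exist, and the rank test can be more powerful.** Both are true. A Hodges-Lehmann estimate with Wilcoxon would also align test and interval, but it would abandon the protocol's chosen effect measure. At log-SD 1.0 the mean-based test rejected in 56.4% of runs against 78.5% for Wilcoxon. That power is for a different question, and a rank p-value does not make a mean difference more certain.

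**Centre.** A reader might infer that ignoring ten centres biases these comparisons, inflates their type I error or costs a known amount of precision. The documents support none of this. Under simple 1:1 randomisation the unadjusted comparison is unbiased and valid, and chance centre imbalance is already reflected in its standard error. The protocol gives no between-centre variance, and a centre term may properly be left to an analysis plan. Its absence is not an error.

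**Conclusion.** The point holds as an internal mismatch in the stated analysis. The protocol selects the test by normality but fixes the estimate as a mean difference, so under Wilcoxon the p-value and interval answer different questions. That Wilcoxon would often be chosen is likely rather than certain: it rests on the expected skew of cost, waiting time and fluoroscopy time and on the discreteness of pain scores. Under the assumed distributions, disagreement ranges from 1.4% of runs to 52.5%.

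Centre adjustment is an optional gain, from about 0.5% to 16% in interval width for assumed variance shares of 1% to 30%.

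A reader might also carry the point over to the main result. It does not reach it: the primary endpoint is a binary event compared by a risk difference against the 0.8% margin, and no formal decision rule rests on the continuous endpoints. The severity is low, and the change is worth making because it is nearly free.

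**What to change.** In Secondary Endpoint Analysis, remove the normality-based choice of test. For each continuous secondary endpoint, prespecify one linear model for the mean with treatment arm as a term and robust standard errors, using the bootstrap for cost. Take the mean difference, its 95% CI and the p-value from that one model; for cost, take the interval and p-value from the same bootstrap. Test and interval then agree. Report median (IQR) as description only.

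As an optional addition, include centre and a short fixed list of baseline covariates from section 5.1, such as age, sex, AF type and CHA2DS2-VASc score. Age and sex already contribute to that score, so the list can be trimmed.

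The cost is a few lines of protocol or analysis-plan wording and of code. No new data are needed, and neither the sample size nor the primary analysis changes.

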## 516 **Missing Data**

- 517 • Primary endpoint: patients lost to follow-up before event occurrence will be  
518 excluded from the per-protocol analysis
- 519 • Sensitivity analyses with imputation may be performed as needed

## 520 **Subgroup and Sensitivity Analyses**

- 521 • Predefined subgroups: age, sex, AF type, CHA2DS2-VASc score, imaging  
522 quality
- 523 • Sensitivity: excluding equivocal imaging cases, or based on procedural  
524 adherence

525 All analyses will be conducted using SAS (v9.4).

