## 2. Introduction

### 2.1 Background and Rationale

Atrial fibrillation (AF) is the most common sustained cardiac arrhythmia, characterized by rapid and irregular atrial electrical activity. This disrupts effective atrial contraction and hemodynamics, leading to blood stasis in the left atrial appendage (LAA) and significantly increasing the risk of thrombus formation. Studies have shown that the incidence of LAA thrombi in anticoagulated patients with AF ranges from 0.4% to 15.2%, depending on individual characteristics and comorbidities. The presence of LAA thrombus is considered an absolute contraindication to catheter ablation. Once detected, the procedure must be postponed until adequate anticoagulation therapy has resolved the thrombus.

Transesophageal echocardiography (TEE) has long been regarded as the gold standard for preprocedural LAA thrombus screening, with a reported sensitivity and specificity exceeding 90%. TEE enables high-resolution imaging by positioning an ultrasound probe in the esophagus, close to the heart. In a global survey of AF ablation centers, 73.2% reported routine use of TEE before ablation, regardless of patients' CHA2DS2-VASc scores. However, despite its diagnostic accuracy, TEE is semi-invasive and associated with discomfort and procedural risks such as gag reflex, sedation-related complications, and even esophageal injury. Additionally, when image quality is suboptimal, the sensitivity of TEE to exclude LAA thrombi is reduced. The proportion of equivocal TEE findings has been reported to be as high as 17.8%, leading to potential misdiagnosis and procedural delays.

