#### 434 **Procedural Data**

- 435       • Imaging modality used (ICE or TEE)
- 436       • Imaging views and interpretation
- 437       • Mapping system and catheter type
- 438       • Transseptal puncture method and anticoagulation strategy
- 439       • Radiofrequency power, ablation duration, lesion characteristics

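### The imaging-quality subgroup and the exclusion of equivocal scans both condition on a result of the randomised modality, so neither is a randomised comparison or a check on the primary result

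*Protocol*

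**What the plan says.** The Protocol's section on subgroup and sensitivity analyses opens its list with "Predefined subgroups: age, sex, AF type". The list goes on to the CHA2DS2-VASc score and ends with imaging quality. The next item reads "Sensitivity: excluding equivocal imaging cases", with an alternative based on procedural adherence.

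Section 4.1 states what is randomised: "Eligible participants are randomly assigned to undergo thrombus screening with either ICE (ICE group) or TEE (TEE group) before catheter ablation". It places allocation after consent and "prior to the start of imaging and ablation procedures".

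In section 5.1 the baseline list contains no image-quality item. "Imaging views and interpretation" appears under procedural data.

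The background (section 2.1) says that poor image quality lowers the sensitivity of TEE. On equivocal scans it says: "The proportion of equivocal TEE findings has been reported to be as high as 17.8%, leading to potential misdiagnosis and procedural delays". No such rate is given for ICE.

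**The concern.** A subgroup analysis keeps the benefit of randomisation when the subgroup is fixed before allocation. Age, sex, AF type and CHA2DS2-VASc score meet that condition; imaging quality does not. Each patient is graded on the modality to which chance assigned them, and the Protocol describes no quality measure common to both devices. Patients with a good TEE image and patients with a good ICE image may therefore be different kinds of patient. A difference between quality strata cannot be read as effect modification.

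The same holds for the exclusion. Dropping equivocal scans may remove different numbers and kinds of patients from the two arms. It also changes the question, because an equivocal scan is part of how a screening strategy performs, and section 2.1 names it as a drawback of TEE. Without those patients, the analysis asks how each modality does when it gives a clear answer. The primary endpoint was chosen to compare the strategies as they are used.

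With very few events expected, a reader could take agreement or disagreement between this analysis and the primary result as evidence, when selection alone could produce either.

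**Working it through.** **Structure**

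1. Section 4.1: allocation precedes imaging, and the modality is what is allocated.
2. Section 5.1: image interpretation is procedural data, and no baseline item measures image quality.
3. Hence imaging quality and equivocal status are post-randomisation results of the assigned modality. Conditioning on them, by stratum or by exclusion, breaks the randomised comparison.

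This conclusion needs no arithmetic. The plan gives no figure for these analyses, so there is none to reproduce. What follows only illustrates size.

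**Inputs**

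- Arm size: 1810 randomised 1:1 (section 2.3), so 905 per arm.
- Expected TEE risk 0.5% (section 3.2), so 0.005 × 905 ≈ 4.5 TEE events.
- Margin 0.8 percentage points (section 3.2).
- Method: Farrington–Manning 95% interval for the risk difference, ICE minus TEE (section 5.4, Primary Endpoint Analysis).
- Equivocal share for TEE: 17.8%, the literature maximum in section 2.1. Applying it to this trial is an assumption.
- Equivocal share for ICE: not given. Values of 0% and 5% are assumed.

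**Numbers removed**

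- TEE: 0.178 × 905 ≈ 161, leaving 744.
- ICE at 5%: 0.05 × 905 ≈ 45, leaving 860.

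**Upper 95% limits, starting from 4 events in each arm**

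| Situation | ICE | TEE | Upper limit |
|---|---|---|---|
| All patients kept | 4/905 | 4/905 | 0.740% |
| 161 TEE patients dropped, no event among them | 4/905 | 4/744 | 0.666% |
| 161 TEE patients dropped, one event among them | 4/905 | 3/744 | 0.781% |
| As above, and 45 ICE patients dropped without an event | 4/860 | 3/744 | 0.838% |

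Only the last row crosses 0.8%. These shifts combine the effect of who is removed with the effect of smaller denominators.

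**Shift in the expected risk difference from selection alone**

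Suppose both arms truly have 0.5% risk overall. Let f be the equivocal share in an arm, and let equivocal cases carry k times the risk of the others in that arm. The risk among non-equivocal patients is then

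r = 0.5% / (1 − f + f·k).

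Example, k = 3:
- TEE, f = 0.178: 0.5 / (0.822 + 0.534) = 0.369%.
- ICE, f = 0: 0.500%.
- Difference created by the exclusion: 0.131 points.

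| k | ICE share 0% | ICE share 5% |
|---|---|---|
| 2 | 0.076 | 0.052 |
| 3 | 0.131 | 0.086 |
| 5 | 0.208 | 0.125 |

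(Points of risk difference against ICE, with the TEE share at 17.8%.)

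The range is 0.05 to 0.21 points, or 6% to 26% of the margin, with no true difference between arms. In this model the shift is zero if k = 1 or if the two shares are equal. It would reverse direction if equivocal reads were commoner with ICE and k were above 1.

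**The case against.** The strongest reply is that these are supportive analyses. The non-inferiority criterion does not refer to them. The mITT population keeps every ablated patient, equivocal or not, and nothing in the text presents the imaging-quality subgroup as causal. A look at interpretable scans can also be clinically useful. All of this stands, and it limits the point to how these two analyses are framed and read.

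A reader might infer that the plan hides a main weakness of TEE. The documents do not support that for the primary result, since equivocal cases that went on to ablation are counted there. In the illustration with more equivocal TEE reads and higher risk among them, the exclusion also moves the estimate against ICE, which is conservative for the non-inferiority claim.

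A reader might also infer that losing a single event through the exclusion reverses the conclusion. Holding both arms at 905 and moving one event does give limits above the margin (4 v 3: 0.837%; 5 v 4: 0.897%). Neither figure models the exclusion: the first leaves the dropped patients in the denominator, and the second adds an ICE event, which an exclusion cannot do. With the 161 TEE patients actually removed, losing one TEE event gives 0.781%, still inside the margin. Crossing it takes a further assumption, such as exclusions in the ICE arm too.

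The 17.8% is a reported maximum. Standardised views, operator training and duplicate blinded reading (section 5.4, Quality Control) may bring it down. At lower assumed rates (TEE 5% with ICE 0%, or TEE 10% with ICE 2%) the spurious shift is about 0.02 to 0.11 points.

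Definitions of equivocal and of the quality categories may properly sit in a statistical analysis plan that is not shown. The objection here is to two analyses that the Protocol states, whichever definitions are used.

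**Conclusion.** The point holds. As written, the imaging-quality subgroup and the exclusion of equivocal cases are non-randomised comparisons, and the exclusion cannot serve as a robustness check of the primary endpoint. This follows from the timing of allocation and is certain on the text.

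The primary mITT analysis is not affected. The size and direction of any bias are unknown, because the ICE equivocal rate and the risk in equivocal cases are not given. Under the assumptions above, selection alone could shift the risk difference by 0.05 to 0.21 points with TEE at 17.8% and ICE at 0% to 5%. A 4 v 4 result could move to an upper limit between 0.666% and 0.838%. These figures show that the supportive analysis could agree or disagree with the primary one through selection; they are not a forecast. The matter should be corrected, but it does not threaten the primary inference.

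**What to change.** In section 5.4, Subgroup and Sensitivity Analyses:

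- Restrict the predefined subgroups to baseline variables: age, sex, AF type and CHA2DS2-VASc score.
- Remove the exclusion of equivocal imaging cases as a sensitivity analysis of the primary endpoint.
- If either imaging-based analysis is kept, label it exploratory and non-randomised.
- Report instead the proportion of equivocal or non-diagnostic screens in each arm with a 95% confidence interval, using all screened patients as the denominator. This addresses directly the TEE problem raised in section 2.1.

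The cost is a wording amendment and one added tabulation. The sponsor should also confirm that the eCRF interpretation item captures equivocal reads, because section 5.1 names no explicit field for them.
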